# Internet-based self-help therapy with FearFighter™ versus no intervention for anxiety disorders in adults: study protocol for a randomised controlled trial

**DOI:** 10.1186/s13063-016-1619-3

**Published:** 2016-10-28

**Keywords:** Anxiety, Randomised feasibility trial, Cognitive behavioural therapy, Internet-based psychotherapy, FearFighter™

## Abstract

**Background:**

Internet-based self-help psychotherapy (IBT) could be an important alternative or supplement to ordinary face-to-face therapy. The findings of randomised controlled trials indicate that the effects of various IBT programmes for anxiety disorders seem better than no intervention and in some instances are equivalent to usual therapy. In Denmark, IBT is part of future treatment plans in mental health care services, but the verification level of the current clinical scientific knowledge is insufficient. The objective of this trial is feasibility assessment of benefits and harms of the Internet-based cognitive behavioural therapy (ICBT) programme FearFighter™ versus no intervention for anxiety disorders in adults.

**Methods and design:**

We will conduct an investigator-initiated, feasibility randomised controlled trial. Sixty-four participants are expected to be recruited via an advertisement posted on the homepage of the Student Counselling Service in Denmark. The inclusion criterion for participation in the trial will be the presence of anxiety disorder as assessed with the Mini International Neuropsychiatric Interview. The exclusion criteria will be suicidal risk, an ongoing episode of bipolar disorder or psychosis, concurrent psychological treatment for the anxiety disorder, considered unable to attend the intervention as planned (due to vacation, work/study placement, sickness, or similar occurrences), or lack of informed consent. The intervention group will be offered nine sessions with the ICBT programme FearFighter™ and a weekly telephone contact to support compliance. The control group will receive no intervention. We define the feasibility outcomes as follows: the fraction of randomised participants out of the eligible people (the lower 95 % confidence interval (CI) ≥ 50 %); and the fraction of compliant participants (those receiving at least six out of nine sessions) in the intervention group (the lower 95 % CI ≥ 60 %). The exploratory clinical outcomes are the number of participants no longer meeting the diagnostic criteria for an anxiety disorder at the end of the trial and level of distress (Beck Anxiety Inventory, Symptom Checklist-90-R, WHO Well-Being Index, Sheehan Disability Scale); the number of severe adverse events; and the occurrence of any psychological treatment outside the trial.

To prevent bias in design, and in the gathering and analysis of data throughout the trial, we will follow the SPIRIT 2013 statement which defines standard protocol items for clinical trials.

**Discussion:**

Based on our findings, we will discuss the feasibility of a future randomised controlled trial examining the benefits and harms of FearFighter™ versus no intervention for anxiety disorders in adults.

**Trial registration:**

ClinicalTrials.gov Identifier: NCT02499055, registered on 1 July 2015.

## Background

Anxiety disorders are characterised by excessive worries and fear of situations, objects, and living creatures. Anxiety disorders can be categorised into generalised anxiety disorder, social phobia, panic disorder, agoraphobia, specific phobias, post-traumatic stress disorder, and obsessive-compulsive disorder [1]. Reviews show that between 14 and 18 % of European citizens fulfil the diagnostic criteria for anxiety disorder according to the *Diagnostic and Statistical Manual of Mental Disorders* (DSM)-III, DSM-IV, or the *International Classification of Diseases, version 10* (ICD-10) [2, 3]. In Denmark, about 350,000 people may be suffering from an anxiety-related disorder [4]. Relatively few people are diagnosed and referred to treatment. In 2005, only 5976 people (under 2 % of the risk group population) were diagnosed with an anxiety disorder and received treatment in Denmark [4].

Cognitive behavioural therapy (CBT) appears to be efficacious in the treatment of anxiety [5] and is the recommended first-choice treatment both by the English National Institute of Health and Care Excellence (NICE) [6] and the Danish Health and Medicines Authority [7]. However, the availability of health care professionals is scarce and cannot cover the demand for traditional face-to-face psychotherapeutic treatment [4]. Therefore, ways for improving the availability of CBT are in demand. A way to save resources is to disseminate psychiatric treatment via different self-administered interventions such as Internet-based self-help psychotherapy programmes [8]. The latest meta-analysis assessing Internet-based self-help therapy (IBT) for anxiety disorders suggests that IBT has a moderate effect size (ES) of 0.79 standardised mean difference (SMD)^1^ on any self-rated symptom measure of anxiety compared with the waitlist control group [9]. IBT compared with face-to-face therapy suggests an ES of 0.05 SMD in favour of face-to-face therapy [9]. With the 2013 revision of the NICE guidelines for anxiety disorders, interventions with self-help resources in England are now recommended in line with face-to-face psychotherapy and pharmacological treatment using a stepped care model for anxiety [8, 10, 11]. In Denmark, IBT is sketched out as part of the future treatment in mental health care services [12, 13], but the current research results are still insufficient [14].

IBT for anxiety disorders is based on the same philosophy as face-to-face CBT and uses the same treatment principles. CBT is a highly structured and standardised treatment [15, 16]. Like CBT treatment manuals a standard Internet-based cognitive behavioral therapy (ICBT) programme consist of 6 to 12 sessions to be completed over 6 to 12 weeks. Each session in ICBT and in CBT contains the same four elements: psychoeducation, exercises and exposure to anxiety-provoking situations, homework (exercises/exposure), and measurement of symptoms. Psychoeducation is prioritised at the beginning of ICBT and CBT treatment programmes, while treatment exposure to anxiety-provoking situations is targeted towards the end.

FearFighter™ is an ICBT programme for the treatment of panic and phobia and it is used in the mental health services in England [8]. Two randomised trials from England have assessed FearFighter™ for patients with an anxiety disorder [17, 18]. Marks and colleagues compared FearFighter™ versus face-to-face behavioural therapy and versus computer-assisted relaxation. Intervention with FearFighter™ was superior to relaxation regarding self-rated anxiety symptoms, while FearFighter™ was equal to face-to-face behavioural therapy [17]. Schneider and colleagues tested FearFighter™ versus Internet-guided minimal CBT plus relaxation for patients with anxiety. No significant difference was found in terms of anxiety severity score between the two interventions at the end of treatment week 10. However, at week 14, significant differences were observed in symptom reduction in five out of ten outcomes favouring FearFighter™ [18].

In Denmark, one randomised trial with FearFighter™ was conducted and published as a nonpeer-reviewed report [19]. The trial compared FearFighter™ with a waitlist control group. The authors found no significant difference between the two groups on the Beck Anxiety Inventory (BAI). The authors reported that due to the chosen eligibility criteria, recruitment was poor and the dropout fraction was high: 50 % in the intervention group and 20 % in the waitlist group. Thus, the trial failed to produce meaningful results. The authors recommended that a new randomised controlled trial be conducted [19]. The objective of the present randomised controlled trial is to assess the feasibility and observe the efficacy of FearFighter™ versus no intervention in people with an anxiety disorder in Denmark.

## Methods/design

### Trial design

The trial is an investigator-initiated, feasibility randomised controlled trial investigating ICBT with FearFighter™ compared with no intervention for adults with an anxiety disorder. We have followed the Standardised Protocol Interventions: Recommendations for Interventional Trials (SPIRIT) 2013 Statement which defines standard protocol items for clinical trials [20]. The Copenhagen Trial Unit (CTU) is responsible for the centralised randomisation. The randomisation is carried out according to a web-based computer-generated allocation sequence with varying block sizes kept unknown to the investigators. Once a participant is assessed as eligible for the trial the trial secretary will use the web-based randomisation system to allocate the participant to an intervention group. The allocation ratio is 1:1. Based on evidence of prognostic factors, the randomisation is stratified into: (1) social phobia and panic with agoraphobia, and (2) panic disorder without agoraphobia and specific phobia [21, 22]. Participants with panic disorder without agoraphobia and specific phobia have a distinctively higher remission rates than other types of anxiety [21, 22]. Assessment will be conducted prior to randomisation and start of intervention (week 0), at post-intervention (week 10), and at follow-up (week 37) (see the flow chart in Figure 1 in the Appendix). The trial has been approved by the Regional Ethical Committee for the Capital Region of Denmark (journal number: H-15005836), and by the Danish Data Protection Agency (journal number; RHP-2015-009 I-Suite 03652). The trial is registered at ClinicalTrials.gov at the United States National Institutes of Health (Identifier: NCT02499055, registered on 1 July 2015).

### Blinding

The trial participants, the support person for FearFighter™, and the administrators of FearFighter™ will be aware of the allocation. Baseline assessment will be conducted before participant randomisation. The assessment of symptoms and recovery at the final interview and at follow-up will be performed by blinded assessors with no knowledge of participant allocation.

Participants will be instructed to withhold information of their allocation group when assessed. Statistical analysis will be conducted blinded with the two intervention groups coded as, e.g. X and Y. Two abstracts with conclusions drawn will be prepared by the blinded investigators, one assuming that X is the experimental group and Y the control group, and one conclusion assuming the opposite [23, 24]. After this, the code will be broken. Analyses and conclusions regarding compliance cannot be blinded and will be kept separate.

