Serious adverse events and other untoward events that require hospitalisation, are life-threatening, or result in death are collected following the SPIRIT recommendations [20]. All adverse and untoward events will be categorised and summated. Finally, the proportion in the groups of experimental and control participants who are compliant with the randomised intervention, defined as the lack of any psychological treatment during the 9-week intervention period, will be registered. At follow-up, it will be registered if participants have been engaged in psychological treatment since the end of the trial, although no restrictions will be imposed on the participants during the follow-up period.

All scores will be compared between the two groups at post-treatment (week 10) and at follow-up (week 37). Serious adverse events and other untoward events will be gathered during the intervention for the intervention group and at post-treatment for both the control and the intervention groups.

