Number of participants complying at least 6/9 FearFighter™ sessions/ randomised participants	Not relevant	Proportion	Test analogous to the above feasibility outcome with the difference that now we want to secure that the sample is not from a population being less than 60 % compliant
Exploratory outcome			
Number of participants who no longer fulfil the diagnostic criteria for an anxiety disorder	MINI	Proportion	Fisher’s exact test and logistic regression adjusted by the protocol-specified stratification variable (the result of the latter test is the primary of the 2 tests)
Severity of anxiety	BAI	Continuous	The general linear univariate model (GLM) taking stratification variables and baseline BAI into account
Psychological distress and psychopathology	SCL-90-R	Continuous	GLM taking stratification variables and baseline SCL-90-R into account
Positive well-being	WHO-5	Ordinal	The proportional odds model for ordinal response taking stratification variables and baseline WHO-5 into account (if conditions are not fulfilled, then nonparametric Mann-Whitney)
Functional impairment	SDS	Continuous	GLM taking stratification variables and baseline SDS into account.
Number of randomised receiving psychological treatment during the 9 weeks	Interview	Proportion	Fisher’s exact test and logistic regression adjusted by the protocol-specified stratification variable (the result of the latter test is the primary of the 2 tests).
Number of participants with one or more adverse event	Interview	Proportion	Fisher’s exact test and logistic regression adjusted by the protocol-specified stratification variable (the result of the latter test is the primary of the 2 tests)

*BAI* Beck Anxiety Inventory, *MINI* Mini International Neuropsychiatric Interview*, SCL-90-R* Symptom Checklist-90 revised, *SDS* Sheehan Disability Scale, *WHO* World Health Organisation

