We have added one additional exploratory outcome, namely the proportion of participants in the experimental and control groups who are compliant with the randomised intervention, defined as the absence of any psychological treatment during the 9-week intervention period. This outcome, as well as the proportion of participants experiencing an adverse event, will be analysed as the other exploratory outcomes with Fisher’s exact test and logistic regression, adjusted by the protocol-specified stratification variable (the result of the latter test is the primary of the two tests). Adverse events will also be reported according to type, severity, and probable relation to the interventions for the two intervention groups.

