## Discussion

The aim of our trial is to investigate the feasibility and observe the efficacy of the ICBT programme FearFighter™ for people with anxiety disorders in Denmark. We expect to widen the scope of this relatively new area of research on Internet-based therapy as the conducted Danish trial on FearFighter™ demonstration project failed to recruit the intended number of participants and suffered from a participant dropout rate of 50 % in the intervention group [19].

Our trial is being conducted in cooperation with the CTU, a centre for clinical intervention research. The design of this trial is in accordance with the guidelines provided by the SPIRIT Statement [20] and the standard operating procedures, developed and maintained by the CTU in order to secure the validity and reliability of the trial results [42]. We have tried our utmost to reduce risks of bias [23, 24, 43–47] by employing centralised randomisation, blinding of outcome assessors, blinding during data management, blinded statistical analyses, and blinded drawing of conclusions to fulfil national and international standards of Good Clinical Practice [48].

Our criteria for inclusion and exclusion are few because we believe that the results of our trial will have a potentially wide generalisability. It should be also noted that the participants will be recruited among visitors to the Student Counselling Service’s homepage. Therefore, we may expect that the participants, students from Danish universities suffering from an anxiety disorder, to be rather homogenous concerning duration and severity of symptoms, age, cultural and economic background, and a low prevalence of comorbidity, which otherwise may limit the generalisability of the results to more clinically heterogeneous samples.

We will consider our feasibility trial sufficiently successful if more than 50 % of the eligible participants are randomised and if more than 60 % of the 32 randomised participants complete FearFighter™. A satisfactory feasibility outcome value will warrant a future large-scale trial to investigate further the observed efficacy and the cost-benefit of FearFighter™.

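### Only compliance is exempted from the X/Y-coded analysis, although one-arm adverse-event reports and relatedness ratings could also reveal the code if they are displayed before both abstracts are written

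*Protocol article*

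**What the plan says.** All references are to the protocol article.

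- **Blinding, coded analysis.** "Statistical analysis will be conducted blinded with the two intervention groups coded as, e.g. X and Y". Then "Two abstracts with conclusions drawn will be prepared by the blinded investigators", one for each possible meaning of the codes, and only afterwards is the code broken.
- **Blinding, the exception.** "Analyses and conclusions regarding compliance cannot be blinded and will be kept separate". No other output is named.
- **Exploratory clinical outcomes, collection.** On when harms data are collected, and in which arm: "will be gathered during the intervention for the intervention group and at post-treatment for both the control and the intervention groups".
- **Table 2, under Statistical analyses.** The adverse-event outcome is "Number of participants with one or more adverse event", tested with Fisher's exact test and a stratification-adjusted logistic regression, as for the other binary exploratory outcomes.
- **Statistical analyses, text after Table 2.** "Adverse events will also be reported according to type, severity, and probable relation to the interventions for the two intervention groups".
- **Abstract, Methods and design.** "The control group will receive no intervention".
- **Discussion.** The bias safeguards listed include "blinded statistical analyses, and blinded drawing of conclusions", with no mention of an exception.

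**The concern.** The Blinding section accepts a sound principle: output that by its nature shows which arm had the programme must stay out of the coded stage. It applies that principle to compliance alone. Two parts of the adverse-event data have the same property. A report taken during the intervention can come only from the experimental arm. A positive rating of relation to a trial treatment can hardly arise in an arm that has no treatment.

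Writing two abstracts protects against slanted interpretation only while the writers do not know which code is which. If a table under code X showed an in-trial report or a related event, the writers would know the allocation when drafting conclusions on remission and on the BAI, SCL-90-R, WHO-5 and SDS scores. At stake is how well the exception to one stated safeguard is drawn, not the validity of the feasibility results.

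**Working it through.** The plan states no figure on this point, so there is none to reproduce. The check is a reading of the sections against each other, followed by two illustrations under assumed rates.

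**1. Which adverse-event output could reveal the code?**

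| Output | Can it arise in the control arm? | Does it identify the arm? |
|---|---|---|
| Number of participants with at least one event (Table 2) | Yes | Not for certain |
| Event type, severity or onset date | Yes: controls are asked at week 10 and can report events from the same weeks | Not for certain |
| Source of report (during the intervention or at week 10) | In-trial source: no (Exploratory clinical outcomes) | Yes, if displayed |
| Positive relation to a trial treatment | No, by inference from the no-intervention control | Yes, if displayed |

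The third row is stated directly in the text. The fourth is an inference, because the protocol speaks of relation to the interventions for both groups. Table 1 marks adverse events in its during-trial column without naming an arm, so the restriction to one arm rests on the outcome text alone.

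**2. Is this output inside the coded stage?** The adverse-event proportion is analysed like the other exploratory outcomes, so its test falls under the coded analysis. For the descriptive breakdown by type, severity and relatedness, the article does not say whether it is produced before or after the code is broken. The Blinding section names only compliance as something to be kept separate.

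**3. How likely is it that a revealing record exists?** Input from the document: 32 experimental participants (Support person and support manual). Assumption: each has, independently, probability p of at least one in-trial or related record. The document gives no p.

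P(at least one record) = 1 − (1 − p)^32

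| Assumed p | Calculation | Result |
|---|---|---|
| 0.5 % | 1 − 0.995^32 | 0.148 |
| 1 % | 1 − 0.99^32 | 0.275 |
| 2 % | 1 − 0.98^32 | 0.476 |
| 5 % | 1 − 0.95^32 | 0.806 |
| 10 % | 1 − 0.90^32 | 0.966 |

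These are probabilities that a record exists. The probability of unmasking is that figure multiplied by the chance that the record is displayed with its source or relatedness in coded output, which is unknown.

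**4. Does the bare count decode the arms?** Assume 32 per arm, the same true event rate in both, and only half of control events captured because controls are asked once.

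| Assumed true rate | P(experimental count higher) | P(tie) | P(control count higher) |
|---|---|---|---|
| 10 % | 0.700 | 0.147 | 1 − 0.700 − 0.147 = 0.153 |
| 20 % | 0.832 | 0.075 | 1 − 0.832 − 0.075 = 0.093 |

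Even with ascertainment this unequal, the higher count gives a hint and not knowledge.

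**The case against.** The strongest reply is that nothing in the article places source or relatedness tables in the coded output. The only adverse-event result tied to a specified test is a binary count, which does not decode the arms. The order in which tables are released is commonly set in an analysis plan that is not shown, and silence on it is no fault. This stands in part: the leak is conditional on display. But the point does not rest on silence. The Blinding section states what cannot be blinded, and that statement leaves out data which the outcome section makes one-sided.

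A second reply is that the rates are arbitrary. This also stands. Part of the outcome text describes events that involve hospitalisation, threat to life or death. If collection is confined to those, rates could be lower still: 0.2 % gives 1 − 0.998^32 = 0.062. Adverse events are also mentioned more generally, so the scope is not settled.

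Three stronger readings are tempting, and the documents do not support them:

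- **That the safeguard does not exist.** Both abstracts must still be written, the tests and covariates are set out in Table 2, and blinding of the outcome assessors is untouched.
- **That one adverse event is enough to unmask.** Controls are asked at week 10 too, so an event or its date alone does not identify the arm.
- **That the high percentages are chances of unmasking.** They are chances, under assumed rates, that a record exists.

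**Conclusion.** The point holds as a minor one. The exception in the Blinding section is drawn too narrowly: by its own logic, in-trial adverse-event reports and relatedness ratings belong with compliance. If either is displayed under the codes, it can disclose the FearFighter arm before both abstracts are final.

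The size cannot be estimated from the document. At assumed rates from 0.5 % to 10 %, a revealing record exists with probability from about 15 % to 97 %, given 32 participants and independence between them, and it matters only if shown. The one-arm collection of in-trial reports is explicit in the text; the one-arm nature of positive relatedness is inferred from the no-intervention control.

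The consequence is limited. Neither feasibility outcome depends on the coding, and the p values for the clinical outcomes serve only to select hypotheses.

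**What to change.** 1. In Blinding, extend the exception: hold adverse-event reports gathered during the intervention, and all relatedness ratings, back with compliance until both abstracts are final.
2. Base the coded X/Y adverse-event comparison on the week-10 data, which are gathered in both arms, and show it without relatedness. This also makes ascertainment more alike in the two arms.
3. Produce the full adverse-event report, including in-trial reports and relatedness, after the code is broken.
4. In the Discussion, qualify the statement on blinded analysis and conclusions to name these exceptions.

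The cost is a few sentences and an agreed order for releasing tables; no data collection changes. There are two downsides. The full harms paragraph is not drafted blind, and the adverse-event outcome is presented in two steps, so the report must say which step each figure comes from.
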